**Fig. 2 Fig2:**
[figure not shown]
Flow diagram of healthcare workers (n) and clusters (m) from recruitment to baseline analysis

### Allocation concealment mechanism

Since the intervention targets whole wards, a complete blinding of participants and consultants in this study is not feasible. All healthcare workers in the intervention clusters, and probably also those in the control clusters, are aware of the allocation to the intervention and control arm, respectively. The consultants delivering the intervention know which clusters were allocated to the intervention arm, but are unaware of which clusters belong to the control arm in the hospitals. In order to reduce the risk of bias resulting from workers being aware to be either in the intervention or control arm, the baseline measurement was conducted before cluster randomisation and implementation of the interventions. In addition, the identification of clusters and the recruitment of participants took place prior to randomisation. Hence, neither the investigators at Ulm University nor the consultants had foreknowledge of the allocation results at the time of participant recruiting and cluster identification. Furthermore, the risk of contamination between intervention and control clusters in the hospitals and elderly care wards was reduced by the clustering of wards according to the specialisation area and the organisational structure of the participating organisations (e.g., separate building areas, different buildings or hospitals). Even though about 6% of participating workers reported working frequently in more than one ward, these workers actually shift between wards belonging to single clusters (e.g., wards within the cluster cardiology), so that there is practically no risk of contamination between the intervention and control arm by the time of random allocation. Survey data collection and analysis, and the process evaluation of the implementation are performed by the authors at Ulm University, independently from both the consultants responsible for delivering the interventions, and the participating healthcare providers. At the end of the study, voluntary wards in the control arm will be given the opportunity to implement the intervention.

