## Methods

### Study design

The study is a two-arm, cluster-randomised intervention with healthcare workers conducted in seven general and three specialised hospitals, and an elderly care centre in Germany, whose wards constitute the clusters. A cluster-randomisation design was required due to the fact that it is an organisational workplace intervention whose main target are wards, and the randomisation of individuals is not feasible, since, in principle, the set of measures implemented in the intervention wards may affect all workers therein. A cluster-randomisation design helps reducing the risk of contamination effects between intervention and control wards and, at the same time, accounts for the correlations of individual measurements being observed within clusters. Outcome data are collected at baseline and at two follow-up times (T1 and T2) in surveys containing validated instruments. Data collection at baseline was performed before the interventions began in the intervention arm. The first follow-up measurement T1 in the single wards will be conducted successively no later than 6 weeks after the implementation of the first measures aiming to reduce the workload of healthcare workers. The final measurement T2 in all wards will be performed 12 months after the last T1 follow-up. Baseline data collection on workers and clients took place between June and December 2019. The follow-up measurements at T1 and T2 will take place in 2020 and 2021, respectively.

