#### Clients

The eligibility criteria for participation in the client surveys were being older than 18 years, being able to give informed consent to participation, being a responsive patient, and having sufficient skills in the German language. Clients (i.e. patients and individuals in elderly care in residencies and at home) are contacted in the participating healthcare organisations and receive a booklet with a brief description of the survey and data privacy information. All clients are required to consent explicitly to participate in the study before data collection. At baseline, T1 and T2 follow-up, approximately 600 patients and 150 individuals in elderly care will be surveyed successively in a cross-sectional design in the intervention and control wards. Participation in the client surveys is anonymous. The outcome data on clients are collected by interviewers either as self-administered questionnaires, or personal interviews upon clients’ request. The interviewers receive a three-hour training in survey methodology provided by the authors from Ulm University before data collection.

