**Individuals in elderly care (*****n*** **= 150)**			
*Age*			0
Age 50–79	42.9	24.2	
Age 80–89	50.0	49.5	
Age 90 and older	7.1	26.3	
*Sex*			0
Male	42.9	28.4	
Female	57.1	71.6	
Years being in elderly care	4.54 (3.74)	3.96 (3.78)	8
*Psychometric scales*			
Trust	3.29 (0.72)	3.76 (0.43)	7
Support	3.07 (0.82)	3.60 (0.45)	9
Decisional control	4.10 (0.89)	4.47 (0.67)	12
Person-focused care	3.19 (1.04)	3.30 (1.20)	10

The estimates of the effective sample size (N_eff_) and the ICC corresponding to the workers’ physical and mental work ability were N_eff_ = 345 and 423, and ICC = 0.05 and 0.01, respectively. The average cluster size in the workers sample was m = 6.53, which yields design effect estimates of DE = 1.29 and 1.05 for the main outcomes. Thus, it will be possible to estimate effect sizes of at least 0.30 and 0.27 at the 80% power and 5% significance levels, for the workers’ physical and mental work ability, respectively. The estimates for the patients dataset were N_eff_ = 234, average ICC = 0.09, m = 19.5, and DE = 2.7. Since data of approximately 1200 additional patients will be collected cross-sectionally at the T1 and T2 follow-ups, a final effective sample size of approximately 234*3 = 702, and an average effect size of about 0.21 concerning patients satisfaction with care may be estimated at the 80% power and 5% significance levels. Finally, the power analysis for the elderly care dataset yielded an average ICC = 0.17, m = 30.7, and DE = 6.32, and an effective sample size of 24 per survey. Thus, for this dataset, at the end of the study, an effect size of about 0.66 can be estimated at the 80% power and 5% significance levels with a final effective sample size N_eff_ = 74 of elderly care clients.

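### The stated safeguard that recruitment preceded randomisation cannot cover clients surveyed at T1 and T2, so the patient satisfaction comparison is open to differential recruitment

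*Protocol article*

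**What the plan says.** Under Allocation concealment mechanism, the article states that "the identification of clusters and the recruitment of participants took place prior to randomisation". From this it concludes that neither the university investigators nor the consultants "had foreknowledge of the allocation results at the time of participant recruiting and cluster identification". Neither sentence is restricted to workers. The same section says that the baseline measurement preceded randomisation, and that staff in intervention wards know their allocation and those in control wards probably do.

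The Participants section covers both workers and clients. Its Clients subsection says that about 600 patients and "150 individuals in elderly care will be surveyed successively in a cross-sectional design in the intervention and control wards" at each of baseline, T1 and T2, anonymously. Eligibility includes being responsive, being able to consent and having enough German. Clients are contacted inside the participating organisations. "The outcome data on clients are collected by interviewers", by questionnaire or, if the client asks, by personal interview.

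On timing, Study design says that "The follow-up measurements at T1 and T2 will take place in 2020 and 2021, respectively", with T1 in each ward "no later than 6 weeks after the implementation of the first measures". The power paragraph in Results confirms that T1 and T2 bring in new people: "Since data of approximately 1200 additional patients will be collected cross-sectionally at the T1 and T2 follow-ups".

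The nearest safeguard is at the end of Allocation concealment mechanism: the university team collects and analyses the survey data independently of the consultants and the providers. The Clients subsection adds a three-hour interviewer training in survey methodology.

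**The concern.** Recruiting individuals before clusters are allocated is the standard protection against selection by arm in a cluster trial. The article invokes it in general terms. For clients it protects only the baseline wave, in which no intervention effect can exist. The waves in which an effect could appear are recruited when the arm of a ward is known, or probably known, to its staff.

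Two features add to the exposure. Some eligibility criteria, such as responsiveness and sufficient German, call for judgement. The client samples are also anonymous and new at each wave, so no client has an individual baseline satisfaction score with which to adjust for who was recruited. Baseline ward averages can correct for stable differences between wards, but not for a change in recruitment after allocation. Imputation cannot recover clients who were never approached.

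If, in one arm, more satisfied clients are approached or agree to take part, the arms will differ in satisfaction without any effect of the intervention.

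**Working it through.** **Order of events**

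1. Baseline preceded randomisation (Allocation concealment mechanism).
2. T1 follows the first measures in the wards. Such measures exist only once intervention wards have been chosen, so T1 comes after allocation. T2 is 12 months after the last T1 (Study design).
3. T1 and T2 clients are new cross-sections (Clients; Results).
4. Hence every T1 and T2 client is recruited after allocation, and the recruitment-timing statement cannot apply to them.

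**The plan's own patient figures, reproduced.** Inputs from Tables 1 and 2 and the power paragraph in Results: n = 632, ICC = 0.09, m = 19.5, DE = 2.7, effective N = 234 per wave, 702 over three waves, detectable effect 0.21.

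- DE = 1 + 0.09 × (19.5 − 1) = 2.67 (stated 2.7).
- Effective N = 632 / 2.7 = 234, as stated; with DE = 2.67 it is 237.
- Detectable effect = 2 × (1.960 + 0.842) / √702 = 0.211, taking a two-sided 5% level, 80% power and equal arms. The stated 0.21 reproduces.

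**Share recruited after allocation**

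- By effective size: 2 × 234 = 468, and 468 / 702 = 67%.
- By raw count: 1200 / (632 + 1200) = 66%.

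**Scale of a possible shift (assumption, not from the documents).** Suppose participation stays at the baseline patient response of about 53%, so that 47% are unobserved. Suppose also that, in one arm only, willingness to take part has correlation ρ with satisfaction under a normal selection model. The mean among participants then moves by ρ × φ(z) / p, in SD units. With p = 0.53, z = 0.075 and φ(z) = 0.398, the multiplier is 0.398 / 0.53 = 0.75.

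| ρ | Shift (SD) | Relative to 0.21 |
|---|---|---|
| 0.05 | 0.04 | 18% |
| 0.10 | 0.08 | 36% |
| 0.20 | 0.15 | 71% |
| 0.30 | 0.23 | 107% |

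If the same selection acts in both arms, the shift cancels. Only a difference between arms matters, and the documents give nothing from which to estimate it.

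**The case against.** The strongest reply is that the sentence was never meant for clients. It follows one about workers knowing their arm and is in the past tense. The abstract describes the participants of the interventions as healthcare workers, and the later client surveys are described in the future tense. A reader might infer that the article makes a plainly false claim; in context, the sentence is probably about workers and true of them. But clients are also described under Participants, and the wording carries no limit. If workers only were meant, the client follow-up simply has no statement of this kind.

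A reader might also infer that interviewers who know the arm recruit the clients. The documents do not say this. They do not state who first approaches clients, who judges eligibility or whether interviewers know a ward's arm.

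Nor is the stage wholly without protection. Data collection independent of the providers bears on selection by ward staff, although it is not masking.

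New samples after allocation are inherent in repeated surveys of patients whose mean stay is about 7 days (Table 2), so the design is not in itself an error. Detailed survey procedure may also stand in a full protocol that is not shown. That answers a complaint about missing detail, but not the unqualified scope of the stated safeguard.

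Three further limits stand. The 53% is a pre-randomisation figure for all patients and shows non-response, not a difference between arms. The baseline age imbalance (54.6% against 38.7% aged 70 and older) arose before allocation and is no evidence of this bias. The elderly-care follow-up samples (about 2 × 150 = 300) add little, because the Discussion already says that the second hypothesis cannot be investigated there.

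**Conclusion.** The point holds in a limited form. The recruitment-timing safeguard is sound for workers and for baseline clients. It cannot extend to T1 and T2 clients, who supply about two thirds of the patient data and all of the post-intervention patient data. Independence of data collection from consultants and providers does not conceal a ward's arm from whoever approaches or interviews clients.

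The patient satisfaction comparison is therefore open to differential recruitment. The documents do not show that it has occurred, and its size is unknown. The range of 0.04 to 0.23 SD rests wholly on assumed one-arm correlations of 0.05 to 0.30 at 53% participation. It shows only that modest selection could be of the same order as the planned 0.21. The primary outcome, workers' work ability, is not affected by this point.

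**What to change.** - In Allocation concealment mechanism, limit the statement on recruitment before randomisation to workers and baseline clients, and say that T1 and T2 clients are recruited after allocation.
- At T1 and T2, have interviewers who are not told the ward's arm approach consecutive or all eligible clients on preset days, without selection by ward staff.
- Log eligible, approached and refusing clients by ward. Compare the arms on these counts and on age, sex and general health.
- Adjust the client follow-up models for age, sex and general health, as the baseline client models already do (Table 4).

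The cost is small: an addition to the existing interviewer training, a simple log and slightly less flexible survey days. Sample size and intervention are unchanged. Masking may sometimes fail in practice, for example if a client or staff member reveals the arm. Covariate adjustment cannot remove selection on satisfaction itself, so the log and the fixed approach rule are the main protection.

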### Statistical methods

The intervention effects on employees’ work ability and clients’ satisfaction with care will be estimated by means of generalised linear mixed-effect (GLM) regression models [17] with two levels of nesting (clusters within healthcare organisations). The GLM models are appropriate for cluster-randomised trials, since they account for the clustered structure of data in a longitudinal design [18]. Missing data at the end of the study will be handled by imputation routines and sensitivity analyses [19, 20]. The mean scores of the psychometric scales will be computed with available items if no more than 30% of the items defining the scale are missing [21]. The ICC at baseline are estimated from the variance components of a random-intercept model with two levels of nesting (clusters within organisations). The baseline data are analysed with a series of GLM Bayesian regression models (also called hierarchical models) by means of Markov Chain algorithms as described elsewhere [22]. The goodness-of-fit was assessed by the Deviance Information Criterion (DIC). Lower values of the DIC statistic indicate a better model fit [23]. Given the role of the effort-reward imbalance as a potential mediating mechanism between the intervention and the main outcomes (see methods section), the associations between physical and mental work ability with effort-reward imbalance and overcommitment are investigated in three regression models with the workers dataset. Due to the fact that health in the work ability concept is thought to be a determining antecedent of one’s own work ability perceptions, the fully adjusted models include two SF12-equivalent physical and mental health component scores [24]. In addition, for the patients dataset, the associations between the four indicators of satisfaction with care and the cluster-levels of psychosocial load of healthcare workers are estimated.

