**Patients (*****n*** **= 632)**			
*Age*			4
Age 18–49	22.9	17.5	
Age 50–69	38.4	27.9	
Age 70 and older	38.7	54.6	
*Sex*			2
Male	47.1	50.0	
Female	52.9	50.0	
Length of hospital stay (days)	7.26 (7.84)	6.90 (7.61)	5
*Psychometric scales*			
Trust	3.71 (0.46)	3.77 (0.38)	4
Support	3.58 (0.57)	3.68 (0.46)	28
Availability	3.57 (0.51)	3.64 (0.44)	2
Decisional control	4.36 (0.56)	4.35 (0.51)	4

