DIC	881		874		773		863		827		793	
Residual variance	0.884		0.874		0.783		0.866		0.831		0.800

**Table 4 Tab4:** Bayesian linear mixed models for the clients datasets (complete cases). The models for the patients dataset are adjusted for age, gender, organisation type (general hospital vs. getriatric and psychiatric hospitals), general health, and education. The models for the elderly care dataset are adjusted for age, gender, general health, and education. Beta: regression coefficient, SE: standard error, and 95% CI: confidence intervals at the 95% level. DIC: deviance information criterion. Effort-reward imbalance (ERI) and overcommitment values correspond to the average of psychosocial load of workers at the cluster level

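### The patient power figure counts the pre-intervention survey wave as evidence on the effect (234 × 3 = 702, giving 0.21), and the effect model gives that wave no other role

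*Protocol article*

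**What the plan says.** - **Effect model (Statistical methods).** Work ability and client satisfaction are both to be analysed with mixed-effect "regression models [17] with two levels of nesting (clusters within healthcare organisations"). The reason given is that such models suit trials like this because "they account for the clustered structure of data in a longitudinal design". No covariate, baseline term or arm-by-wave term is named, and none is ruled out. Imputation and sensitivity analyses are planned for missing data at the end of the study.
- **Client surveys (Participants, Clients).** About 600 patients and 150 elderly-care clients per wave "will be surveyed successively in a cross-sectional design in the intervention and control wards". Also, "Participation in the client surveys is anonymous", so no client can be linked from one wave to the next.
- **Timing (Allocation concealment mechanism).** "the baseline measurement was conducted before cluster randomisation and implementation of the interventions".
- **Power (Results, paragraph after Table 2).** For patients at baseline: effective sample size 234, average ICC 0.09, mean cluster size 19.5, design effect 2.7. Because T1 and T2 will add about 1200 patients, the final effective size is put at 234 × 3 = 702 and the detectable effect at about 0.21. For elderly care the effective size is 24 per survey, 74 in total, with a detectable effect of about 0.66.
- **Baseline arms (Table 2).** The share in the row "Age 70 and older" is 38.7% in control and 54.6% in intervention. Trust, Support and Availability are higher in the intervention arm.
- **Baseline models (Table 4 legend).** "The models for the patients dataset are adjusted for age, gender, organisation type", general health and education. The article does not say whether this set carries over to the effect analysis.

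**The concern.** The factor of three treats the baseline wave as a third batch of outcome data on the intervention. Before the intervention there is no effect to observe, so that wave can only describe where the wards started. That is its value here: clients are anonymous and new at each wave, so no within-person baseline exists, and pre-existing ward differences can be removed only through the baseline wave or client covariates.

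Two things are at stake. The quoted detectable effect of 0.21 is too optimistic. And if the analysis followed the power sum and took one arm contrast over all three waves, that contrast would mix a diluted effect with whatever ward differences persist. Client satisfaction is the secondary outcome and the second of the trial's two hypotheses.

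**Working it through.** **1. Reproduce the stated figure.** With equal arms, 80% power and a two-sided 5% level (sidedness assumed), the detectable standardised effect is (1.960 + 0.842) × 2/√N_eff = 5.603/√N_eff.
- Design effect: 1 + 0.09 × 18.5 = 2.67, stated as 2.7. Then 632/2.7 = 234.
- N_eff = 702: 5.603/26.50 = **0.211**, the stated 0.21.

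**2. Remove the pre-intervention wave.**
- T1 + T2: 2 × 234 = 468, and 5.603/21.63 = **0.26**.
- Elderly care: 3 × 24 = 72 gives 0.66, the stated figure (the stated total of 74 gives 0.65). T1 + T2: 2 × 24 = 48 gives 5.603/6.93 = **0.81**.

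**3. What pooling would estimate.** Let g be a persistent arm difference and d the true effect at both follow-ups. Over three equal waves the arm contrast averages (g + (g + d) + (g + d))/3 = g + (2/3)d. With g = 0 and d = 0.21 this is 0.14. Any persistent g passes through in full.

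**4. Size of the observed baseline gaps (Table 2; SD is the root mean square of the two arm SDs).**

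| Scale | Raw gap | SD | Raw gap in SD | Table 4 gap (SE 0.09) | In SD |
|---|---|---|---|---|---|
| Trust | 0.06 | 0.42 | 0.14 | 0.03 | 0.07 |
| Support | 0.10 | 0.52 | 0.19 | 0.06 | 0.12 |
| Availability | 0.07 | 0.48 | 0.15 | 0.04 | 0.08 |
| Decisional control | -0.01 | 0.54 | -0.02 | -0.01 | -0.02 |

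Age 70+: 54.6 - 38.7 = 15.9 points.

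The patient split by arm is not given in the text. With a design effect of 2.7 and an assumed intervention share of 25% to 60%, the first three raw gaps have z of about 0.9 to 1.5. The age gap has z of about 2.3 to 2.4 for shares of 33% to 50%, if the same design effect applies to age.

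**5. If the same wards return and their effects persist.** Adding effective sizes across waves assumes that the waves are independent. Let s be the correlation of true ward effects between waves; s = 0.7 to 0.9 is an assumption, as the article gives no value.
- Variance of a ward mean, one wave: 0.09 + 0.91/19.5 = 0.137.
- Over T1 + T2: 0.09(1 + s)/2 + 0.91/39 = 0.100 (s = 0.7) or 0.109 (s = 0.9).
- N_eff = 234 × 0.137/0.100 = 320, or 234 × 0.137/0.109 = 294. Detectable effect 0.31 to 0.33.
- Adjusting for the ward's baseline mean multiplies this variance by 1 - r², where r² = (0.09s)²/(0.137 × two-wave variance) = 0.29 or 0.44. N_eff becomes about 452 or 526, and the detectable effect about 0.26 or 0.24.
- For a single follow-up wave, r = 0.09s/0.137 = 0.46 to 0.59. The standard error falls by 11% to 20%, and N_eff rises from 234 to about 297 to 361.

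These step 5 figures are illustrative only. They show that the baseline wave does contribute precision, but as an adjustment and not as a third sample.

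**The case against.** The strongest reply is that 234 × 3 is a rough power sum and not an analysis specification. The analysis section speaks of a longitudinal design, which is compatible with a three-wave model containing an arm-by-wave term, and such a model would deal with persistent ward differences. A condensed article normally leaves covariates to the full protocol or analysis plan. This stands as far as it goes. A reader might infer that the effect model excludes case mix and the ward's baseline value; the article does not say so, and its silence cannot be counted as a defect. The reply does not rescue the 0.21, because no valid use of the baseline wave turns it into a third sample of outcome data on the effect.

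Three other strong readings are tempting and unsupported.
- **The raw gaps show bias.** They are compatible with chance, and every Table 4 interval covers zero (Trust: -0.16 to 0.22). The age gap is more marked, but no figure in the article shows that age drives satisfaction here. Chance is not the only candidate, since the first ten hospital intervention clusters were drawn with probability proportional to size. That case mix follows ward size is conjecture.
- **Case mix explains the fall from raw to adjusted gaps.** The Table 4 patient models also contain ward-level work ability, effort-reward imbalance and overcommitment. They weight wards differently from raw means and use 577 complete cases out of 632. The fall cannot be assigned to case mix.
- **Survey mode differs by arm.** Clients answer "either as self-administered questionnaires, or personal interviews upon" request, and the intervention arm is older, but the article reports no mode by age or arm.

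It is also not stated that the same wards are surveyed at each wave, so step 5 is conditional on that.

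**Conclusion.** The point holds in this form: the article counts pre-intervention clients as information on the effect, and nothing in the effect model gives them another role. By the article's own method the patient detectable effect is about 0.26 and not 0.21, before any gain from baseline adjustment. This rests on equal arms, a two-sided 5% level and independent waves. If ward effects persist, the unadjusted figure is larger: 0.31 to 0.33 under the assumed correlations. The elderly-care figure moves from 0.66 to about 0.8, for a dataset that the Discussion already says cannot address the second hypothesis.

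The harm to the estimate is conditional. Dilution to two thirds and carry-through of ward differences would follow only if the waves were pooled as the power sum implies. Observed raw gaps of 0.14 to 0.19 SD on three patient scales show why the choice matters; they do not show that bias exists. The change should be made, but it concerns the secondary outcome and leaves the primary analysis of work ability untouched.

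**What to change.** 1. Define the client effect as the arm contrast at T1 and T2.
2. Use the baseline wave only as an adjustment. Either include it in the model with the arms constrained equal at baseline, or adjust for the ward's baseline mean of the same scale where one exists. The two are not interchangeable when ward sizes differ or a ward has no baseline clients, so one should be named as the main analysis.
3. Name the client covariates already used in Table 4: age, gender, general health, education and, for patients, organisation type. Handle missing covariates under the imputation already planned, as the complete-case baseline models lost 632 - 577 = 55 patients.
4. Restate the detectable effects from the follow-up waves only: about 0.26 for patients and about 0.8 for elderly care before baseline adjustment. Add a range for persistence of ward effects if the same wards return.

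The cost is wording and a recalculation. The baseline wave and the covariates are already collected, and no new data or design element is needed.
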